# SAFETY MONITORING

This study is not an intervention study. However, a major component of safety monitoring is ascertainment and reporting of adverse events, including adverse reactions to study procedures. The approach to these activities for this trial is summarized in the sections that follow. Adverse events will be defined by standard nomenclature as defined below.

- 1. Adverse Event, Serious Adverse Event, and Unanticipated problems Definitions
     1. Adverse Event (AE)

An adverse event (AE) is any untoward medical occurrence in a subject, including any abnormal sign, symptom, laboratory abnormality or disease, temporally associated with the subject’s participation in the research, whether or not considered related to the subject’s participation in the research. (21)

- 1. Unanticipated Problems

OHRP considers unanticipated problems, in general, to include any incident, experience, or outcome that meets all of the following criteria:

- Unexpected (in terms of nature, severity, or frequency) given the study procedures that are described in the protocol related documents, such as the IRB approved research protocol and informed consent and assent documents; and the characteristics of the subject population being studied;
- Related or possibly related to participation in the research (possibly related means there is a reasonable possibility that the incident, experience, or outcome may have been caused by the procedures involved in the research; and
- Suggests that the study places subjects or others at a greater risk of harm (including physical, psychological, economic, or social harm) than was previously known or recognized.

If the answer to all three questions is yes, then the event is an unanticipated problem and must be reported to appropriate entities (22). To assess these three questions requires that events be classified as to seriousness, expectedness, and potential relationship to the study participation.

- 1. Classification of Adverse Events Documentation

Monitoring adverse events requires that they be classified as to intensity, expectedness, and potential relationship to the study procedures. All adverse events occurring within 24 hours of the signing of the informed consent, regardless of intensity, expectedness or causal relationship, will be recorded.

- 1. Adverse Event Intensity

Intensity of an adverse event will be defined as follows:

Mild (1): Awareness of event, but easily tolerated

Moderate (2): Discomfort enough to cause some interference with daily activities

Severe (3): Inability to perform normal daily activities

- 1. Serious Adverse Event Intensity

A serious adverse event is any untoward medical occurrence that:

1. Results in death.
2. Is life threatening (refers to an event in which the subject was at risk of death at the time of the event; it does not refer to an event which hypothetically might have caused death if it were more severe).
3. Requires hospitalization or prolongation of existing hospitalization.
4. Results in persistent or significant disability/incapacity or
5. Results in a congenital anomaly/ birth defect.
6. A medical event that may not be immediately life-threatening or result in death or hospitalization but that may jeopardize the subject or may require intervention to prevent a serious outcome, may also be considered serious (e.g. intensive treatment in an emergency room or at home for allergic bronchospasm; blood dyscrasias or convulsions that did not result in hospitalization; or development of drug dependency or abuse). Medical and scientific judgment must be exercised when classifying events as serious.
   1. Adverse Event Expectedness

All adverse events will be evaluated as to whether their occurrence was expected.

**Unexpected**: An unexpected adverse event or adverse reaction to study procedures is one for which the nature or severity is not consistent with either:

1. Known information associated with the procedures and described in the protocol, consent/assent form, and other relevant sources of information; or
2. The expected natural progression of any underlying disease, disorder, or condition of the subject(s) experiencing the adverse event and the subject’s predisposing risk factor profile for the adverse event.

**Expected**: An event is considered expected if is known to be associated with the study procedures or the expected natural progression of the subjects’ underlying disease or condition. For this protocol, expected events include the following.

1. In the subjects with SMA:
   1. Fatigue
   2. Respiratory change or respiratory event
2. In subjects of this age range:
   1. Bruising at phlebotomy site
   2. Adverse Event Causality

All adverse events will be assessed as to determine causality

1. Not related: The event is clearly related to other factors, such as the subject’s clinical state, or non-study procedure.
2. Possibly related: The event follows a compatible temporal sequence form the time of the study procedure, but could have been produced by other factors such as the subject’s clinical state or non-study procedure.
3. Probably related: The event follows a reasonable temporal sequence form the time of the study procedure, and cannot be reasonably explained by other factors such as the subject’s clinical state or non-study procedure.
   1. Adverse Event Reporting
   2. Unanticipated Problems

In monitoring adverse events, it is essential to determine whether an adverse event represents an unanticipated problem (i.e., meets all 3 criteria specified in Section 8.1) that needs to be reported to appropriate entities based on OHRP guidelines (23). The institution at which the subject experienced an adverse event determined to be an unanticipated problem must report to the OHRP.

- 1. Adverse Events

All adverse events will be captured for a 24 hour period starting from the time the subject signs informed consent. All events will be reported within 7 days of notification of the event. All serious adverse events will be assessed by a qualified medical monitor appointed by the Coordinating Center.

- 1. Serious Adverse Events:

All serious (i.e. not fatal or not life-threatening) adverse events that are unexpected and considered possibly or probably related to the study procedure will be reported to the Coordinating Center within 7 days of learning of the event. All fatal or life-threatening adverse events are to be reported to the Coordinating Center within 24 hours of learning of the event.

If the serious, unexpected adverse event is associated with study procedures, the Coordinating Center will notify the appropriate regulatory agency (ies) and all participating investigators on an expedited basis. It is the responsibility of the investigator to promptly notify the Institutional Review Board/Independent Ethics Committee (IRB/IEC) of all adverse events according to local IRB/IEC policies.

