# STUDY DESIGN

This study will be a multi-center, pilot study enrolling 120 subjects, age 2 to 12 years from approximately 15 academic pediatric neuromuscular clinics. Primary care pediatric practices within these institutions may refer patients for the controls. Participating clinic sites will have the laboratory support to process the blood and urine samples appropriately for shipment to central laboratory and biomarker analysis.

Each subject will be seen for a single visit, during which an assessment of functional ability, pulmonary status and nutritional status will be performed. In addition, blood and urine specimens will be collected for biomarker assessment and DNA specimens collected for SMN2 copy number. SMN1 genotyping will only be conducted on control subjects who are genetically unrelated to SMA children. Control subjects have the option to decline the DNA (SMN1 gene analysis) portion of the study. No therapeutic intervention will occur.

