# STUDY PROCEDURES

- 1. Informed Consent / Informed Assent

Signed and dated IRB-approved informed consent must be obtained from the subject’s parent or guardian before any study-specific screening procedures are performed. The Principal Investigator or approved designee will obtain informed consent from the parent or guardian and an informed assent from the pediatric subject (according to local institutional IRB guidelines) after full review of the pros and cons of the study. The possible benefits and complications of participation will be explained in detail. Every effort will be made to ensure that the subject and parent/guardian fully comprehend the nature of the study and the details of his or her participation. A copy of the consent form will be provided to the parent/guardian and subject. The informed consent process must be documented in the subject’s medical chart.

- 1. Schedule of Study Measurements

Subjects will be screened for eligibility according to the inclusion/exclusion criteria and then will be enrolled and have additional study evaluations on the same day. The purpose of the screening is to identify eligible subjects and to eliminate evidently unsuitable subjects before the enrollment process is started. In some instances, at the site’s discretion, the screening may occur on a separate day than study procedures (for example to confirm carrier status of siblings of SMA subjects). It is anticipated that the duration for all the screening and study procedures will be between 2-4 hours.

- 1. Screening Procedures

Each clinical site will maintain a Screening Log of all subjects screened for the trial. This log will record the reason for any screen failure. Confidentiality of subject data will be maintained throughout the trial. No patient identifiers will be used and all data entered into the trial database will be under code.

All screening procedures are the same for the SMA subjects and the control group.

1. Medical review of inclusion and exclusion criteria.
2. Temperature.
3. Those subjects deemed eligible by the Principal Investigator or designee will complete additional evaluations for Enrollment.
   1. Study Procedures

All study procedures are the same for the SMA subjects and the control group with the exception of collection of DNA for SMN1 genotyping for control subjects only (refer to 6c below).

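### Adverse event capture runs for 24 hours from consent, so for subjects who consent on an earlier day it can end before the study blood draw and tests

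*Protocol*

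**What the plan says.** Two places in the protocol fix the recording period, both counted from consent. Section 8.10: "All adverse events will be captured for a 24 hour period starting from the time the subject signs informed consent". Section 8.3: "All adverse events occurring within 24 hours of the signing of the informed consent, regardless of intensity, expectedness or causal relationship, will be recorded". No other section restarts or extends the clock on the day of the procedures.

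Section 6.1 requires the parent or guardian to sign consent "before any study-specific screening procedures are performed". Section 6.2 gives the usual schedule, in which subjects are screened and "then will be enrolled and have additional study evaluations on the same day". It then adds an exception that each site may choose to use: "the screening may occur on a separate day than study procedures (for example to confirm carrier status of siblings of SMA subjects". No limit is set on the interval between the two days.

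Section 6.3 lists an eligibility review and a temperature reading as screening. Section 6.4 lists the blood and urine collection, motor assessment, timed walk and spirometry as study procedures. The opening of Section 8 includes reactions to study procedures in the aim of safety monitoring. Section 8.6 names bruising where blood was drawn as an expected event for subjects of this age.

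**The concern.** The events this study can cause come from its procedures, but the recording period is tied to a signature. The two coincide only when consent and procedures fall on the same day or close to it. Section 8.7 judges causality by timing relative to the study procedure, so capture and causality run on different clocks.

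On the separate-day pathway the rule requires recording during a period in which only an eligibility review and a temperature reading may have happened. It can then stop requiring it before anything that might cause a reaction. The pathway's named example is sibling controls, who are healthy children; section 11.4 acknowledges that control subjects do not benefit directly. Section 8.9 also identifies unanticipated problems through the monitoring of adverse events, so an event never captured may not reach that assessment.

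**Working it through.** No sample size, power or error rate is involved. The check is a timeline.

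**Inputs**
- Capture window: 24 h from signing of consent (sections 8.3 and 8.10).
- Consent precedes study-specific screening (section 6.1).
- Usual visit: "It is anticipated that the duration for all the screening and study procedures will be between 2-4 hours" (section 6.2).
- Interval from consent to procedures on the separate-day pathway: not stated (section 6.2). The values below are assumptions.

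**Formula**

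Capture left after procedures = max(0, 24 h − time from consent to end of procedures)

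**Results**

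| Pathway | Consent to end of procedures | Capture left |
| --- | --- | --- |
| Same day, short visit | 2 h | 24 − 2 = 22 h |
| Same day, long visit | 4 h | 24 − 4 = 20 h |
| Separate day (assumed) | 20 h | 24 − 20 = 4 h |
| Separate day (assumed) | 24 h | 24 − 24 = 0 h |
| Separate day (assumed) | 48 h | max(0, −24) = 0 h |
| Separate day (assumed) | 7 days = 168 h | max(0, −144) = 0 h |

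The same-day rows assume that consent is signed at the start of the visit. The 20 h row shows that a different calendar day is not automatically outside the window: an afternoon consent followed by procedures the next morning leaves a few hours. Once procedures start 24 h or more after consent, the window has closed before the study's own blood draw. A wait for a carrier result could plausibly be that long, but the protocol gives no figure.

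**Reading the sections together.** Sections 6.1 and 6.2 permit consent on one day and procedures on a later one. Sections 8.3 and 8.10 end the required recording 24 h after the first of these. Nothing reconnects recording to the second, so following every section as written can leave the procedures outside the window.

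**The case against.** The strongest reply is that this is an exception. Section 3 says "Each subject will be seen for a single visit", section 6.2 makes same-day evaluation the norm, and the norm is well covered. That stands and limits the scope. It does not remove the gap, because section 6.2 expressly allows the other pathway.

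The gap also needs consent to be signed on the earlier day. Carrier testing of siblings is not listed as a study test, and the protocol does not say whether carrier status comes from existing records or is obtained under study consent. The scenario is therefore permitted by the text, but the text does not show how often it would occur.

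Several stronger readings are tempting, and the protocol does not support them:
- **All procedure-related events would be lost.** Section 8.11 times the reporting of serious, unexpected, related events, and of fatal or life-threatening ones, from when they are learned of, with no 24-hour limit. Unanticipated problems and notification to the ethics committee are separate duties as well. The gap is clearest for non-serious events.
- **All 20 controls are affected.** Twenty is only the size of the control group. Controls may be unrelated children, and no sibling share is given. Section 6.2 offers siblings only as an example, so some SMA subjects could be affected too. The number is unknown in both directions.
- **Fatigue and respiratory events would be missed in siblings.** Section 8.6 lists these as expected only in subjects with SMA. For controls the listed expected event is bruising.
- **Safety results would be biased.** The statistical section describes no adverse event analysis, so there is no planned summary whose bias could be assessed.
- **20-22 hours after a same-day visit is too short.** Nothing in the protocol contradicts that length, and it is the sponsor's choice.

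**Conclusion.** The point holds, within narrow limits. Sections 8.3 and 8.10, read with sections 6.1 and 6.2, allow required adverse event recording to end before the study procedures begin. This is a fixed rule that fails Section 8's own aim on a pathway the protocol permits; it is not a detail left for another document.

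The conclusion rests on two conditions: consent is signed on the earlier day, and the procedures start 24 hours or more after it. A shorter gap leaves partial coverage. The consequence is that non-serious procedure-related events need not be recorded for an unknown number of subjects. No primary or secondary objective is affected. The study is non-interventional and describes its risks as minimal, so this is a modest correction to safety ascertainment and no threat to the study's conclusions.

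**What to change.** Reconcile sections 6.2, 8.3 and 8.10. Define adverse event capture as running from signing of consent through a stated period after the last study procedure, and use identical wording in 8.3 and 8.10. The length is for the sponsor to set; keeping 24 hours, counted from the last procedure, would preserve the sponsor's own figure. At the same time, align the single-visit statement in section 3 and the synopsis with the separate-day option in section 6.2.

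The cost is a short wording amendment with the ethics approval that section 12.3 requires. Follow-up for adverse events would end later for separate-day subjects, by the gap between consent and the end of procedures. If 24 hours is kept, same-day subjects gain only the 2-4 hours of the visit. The change belongs before enrollment, since events missed in a study with so little later contact cannot be reliably recovered.

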# TERMINATION OF STUDY PARTICIPATION

Subjects may be withdrawn from the study for the following reasons:

- Subject (or legal guardian) declines further study participation.
- In the investigator’s judgment, it is in the subject’s best interest.

# TRAINING AND DATA MANAGEMENT

- 1. Training Description

The Coordinating Center will provide a central protocol training session for all the PIs and study coordinators (and OTs or PTs if they will be performing the Modified Hammersmith Functional Motor Scale assessment). The training session will include using real subjects or video on anthropometric measurements and the Modified Hammersmith Functional Motor Scale assessment, 10-meter Timed Walk Test (ambulatory subjects only) and spirometry testing to ensure consistency and quality across clinic sites. Hands-on training on the Coordinating Center’s web-based Advance Data Entry and Protocol Tracking (ADEPT) system will also be conducted for all study coordinators. Study coordinators must successfully complete an ADEPT certification package at the end of the training session prior to gaining access in ADEPT to ensure database proficiency. The Coordinating Center will conduct on-site in-person training sessions for PIs and study coordinators who are unable to attend the central training session. As accuracy of the specimen handling is essential to achieve study goals, training on proper collection, handling, storage and shipping of blood and urine specimens will be provided during the central training session or at participating sites. All key site personnel who handle and prepare the specimens will be trained by the Central Laboratory and monitored by the Central Laboratory and the Coordinating Center.

- 1. Data Management and Quality Control

A customized data management system will be developed for this study using the Coordinating Center’s Web-based Advanced Data Entry and Protocol Tracking (ADEPT) system. ADEPT is a customizable, secure, web-based system with an Oracle relational database engine, which allows direct data entry from multiple study sites. Information entered into the data entry system will be by subject study identification number; names will not be linked with subject data in the database. Sites will maintain records in secure areas linking the subject name with the identification number assigned for the study. Sites will have full access to their own data and be able to view these data remotely. Study staff will not be able to view subject data associated with other sites. Users associated with the SMA Foundation will have access to cross-site aggregate data. The Coordinating Center’s ADEPT software is designed to be compliant with 21 CFR Part 11 (24).

The data management system for the study will integrate all aspects of study data collection including:

- Participant screening and enrollment data.
- Web-based entry and on-line editing of all study related CRFs.
- Electronic signing of CRFs by site PIs.
- Matching cases and controls.
- Enforcing group balance requirements within sites.
- Collection, processing and tracking of specimens and results to the Central laboratory where specimens will be stored and batched until final distribution to the genomic laboratory and biomarker laboratory (see Specimen Collection Management in protocol section 10.3 and the Manual of Operations).
- Uploading genomic and biomarker results.
- Provide real-time reports on enrollment, data quality, protocol violations, etc. to the sponsor.

Sites enter data via a customized ADEPT secure web application. This system has been specifically designed to support reliable secure data entry for clinical research purposes. The system provides real-time field level validations, context sensitive help and automatic query generation. Data entry forms use browser based logic to enforce proper validations of all data fields and proper skip patterns within study data forms. Interim background data submittals prevent loss of data due to interruption of internet connections.

[figure not shown]

Figure 1. Data Management System

- 1. Data Entry and Editing

The data entry system will include a number of standard features designed to ensure consistently high quality data. Each question on the study form will be associated with a validation, and validations will be executed in real-time during data entry. If a response to a particular question falls outside the range of allowable values specified in the validation for that question, the user will be alerted so that the error can be corrected immediately. Validations will include both inter- and intra-instrument data checks. In addition to alerting the user to invalid entry of items, edit reports will be automatically generated at the completion of data entry for a form. These edit reports will provide the information necessary to investigate any data entry errors or resolve questions regarding out-of-range or questionable values. Edits reports will list subject I.D. number, instrument name, and a detailed description of why each specific data item was flagged. These edits reports can be printed out and reviewed by a supervisor, and returned to the data collector for resolution.

- 1. Case Report Form Completion

CRFs must be completed for each screened and enrolled study subject. It is the investigator’s responsibility to ensure the accuracy, completeness, legibility and timeliness of the data reported in the subject’s CRF. All CRF entries should be derived from, and consistent with, source documentation. Any discrepancies should be explained. Source documentation should indicate the consenting process, the subject’s participation in the study and should document the dates and details of study procedures, adverse events and subject status.

- 1. Specimen Collection Management

Ensuring the accuracy of blood and urine specimens for this trial is paramount. The Coordinating Center and the Central Laboratory have quality control methods in place to ensure this accuracy. Aliquot tubes are linked, and tracked to allow tracing back to the original parent tube. The complete electronic chain of custody has in place will allow the SMA data management system to monitor and report on the critical processes involved in specimen collection, shipping and results. There is immediate feedback between the clinical site, the Coordinating Center and the Central Laboratory when a shipment of specimen samples is sent from the clinical site and the Central Laboratory receives these samples. The final shipment of specimens to the genomic laboratory and biomarker laboratory is also closely monitored for any discrepancies and damage. Reports will be programmed to show by specimen type:

- Count and % specimens compliant with specimen collection.
- Count and % specimens compliant with specimen processing and aliquotting.
- Count and % specimens successfully shipped from sites.
- Count and % specimens received intact by central lab.
- Count and % specimens with successful receipt of corresponding results from biomarker lab.

- 1. Training on Specimen Collection:

ADEPT automatically generates manifests used by sites during the shipping processes. Manifests list the specimens available at the site for shipment. Upon confirmation of shipment, an electronic version of the manifest is forwarded to the central lab, where receipt is also electronically confirmed. For each confirmed specimen at the central laboratory, the data management system will anticipate an appropriate set of results.

Sites will be required to enter the following data into ADEPT:

- Specimen collection date, time, and volume.
- Specimen processing completion date, time, and processing temperature
- Sample storage date, time, and temperature prior to shipment.
- Sample shipment date, time, and temperature.

ADEPT will alert the site if any of the parameters entered are out of range or invalid.

- 1. Data Security and Integrity

The Web-based components of the data management system utilize several levels of security to ensure privacy and integrity of the study data as noted below:

- Web access to ADEPT requires use of assigned user names and passwords.
- Passwords are changed every 90 days.
- Web-based data entry uses secure socket layer (SSL) data encryption.
- Access to any study-specific system features are controlled by Oracle database rights and privileges.
- A full Oracle back up is done on a daily basis and stored offsite.
- Duplicate NT servers are available to replace Oracle or Web Server.
- Primary Identification is via study I.D.
- Access to electronic linkage limited by Oracle Database Administrator.
- Access to hard copies linkage kept in locked cabinets by Clinical Center Coordinators.
- The Coordinating Center firewall limits which internet protocols are allowed to access the Web server.
- No direct access is allowed to the Oracle server from the internet.
- The Coordinating Center’s firewall monitors for unusual (hacker) activity and automatically notifies the Coordinating Center IS staff.

All study data will be stored on the Coordinating Center’s Microsoft NT-based, Oracle server. Access to data on this server (from both inside and outside the data center) is controlled by Oracle’s extensive security features. The Oracle archiving and back-up system ensures minimal data loss, even in the most catastrophic system failure.

